
### Reference standard (occurrence of MACE)

2.3

We use a delayed-type reference test in which our primary clinical outcome is the occurrence of MACE within 6 weeks from the index consultation (see Textbox 2). A 6-week window was selected to enhance comparability with previous research on MACE after presentation with chest pain in Dutch primary care [22]. MACE is a well-established endpoint accepted by regulatory agencies that captures the overall cardiovascular risk rather than focusing solely on one clinical syndrome. MACE is a composite endpoint, consisting of ACS, urgent coronary revascularization and/or all-cause death. ACS is defined as the occurrence of ST-elevation myocardial infarction (STEMI), non-ST-elevation myocardial infarction (NSTEMI), or unstable angina. Secondary outcomes are (I) the occurrence of (non)fatal myocardial infarction (STEMI or NSTEMI), (II) any hospitalization for a cardiovascular cause (e.g. heart failure, atrial fibrillation, aortic pathology, pulmonary embolism) and (III) all-cause death.

### Study flow

2.4

#### Index contact

2.4.1

The study workflow is described in Fig. 2, Fig. 4. In short, during the consultation the patient receives information about the study's objectives, procedures, potential risks and benefits, and decides on their participation. Upon agreement, initial informed consent is obtained by the treating physician, and hs-troponin POCT is conducted by a trained (triage) nurse. While the POCT runs, the GP completes the ‘*chest pain assessment form*’. Subsequently, the GP determines the treatment plan ((e.g. discharge with safety-net advice (‘watchful waiting’), consulting a cardiologist or referral to the hospital for further assessment)). At all times, the GP's own clinical judgement serves as the guiding principle in the management following the consultation. For safety reasons, urgent referral is advised in cases of high clinical suspicion of ACS, hs-troponin POCT values ≥ 4 ng/L, and/or an abnormal ECG (if performed), in line with the HEART-GP strategy recommendations. Additionally, GPs are informed to refer all patients with troponin levels exceeding the overall 99th percentile of 22.9 ng/L. Patients who refuse study participation receive routine care only, which focuses on history taking, physical examination and, based on the discretion of the GP, potentially an ECG, as this is not a part of the standard work-up of chest pain in Dutch primary care [6].

**Fig. 4 fig4:**
[figure not shown]
Study flow at index consultation ∗HEART-GP study forms include the following: pocket card ‘HEART-GP study’ for healthcare professionals, registration form, Chest pain assessment form, Informed consent form, retour envelope, Patient Information Form (PIF) and an accompanying letter. ∗∗Initial informed consent is asked during index consultation, the patient is offered the following information beforehand. *“This out-of-hours primary care center is conducting research involving patients experiencing ‘chest pain’. As part of the HEART-GP study, you will be asked a few additional questions about your symptoms, and an additional finger-stick test will be performed. This test helps to assess whether further diagnostic evaluation at the hospital may be necessary. Please note: the test does not itself diagnose a heart attack. A result exceeding* 4 ng/L*, does not allow for the definitive exclusion of a heart attack. If you agree to participate, the fingerstick test will be conducted and the research team will contact you shortly. They will request your formal informed consent. You may withdraw from the study at any time without consequences. Your personal information will be treated with strict confidentiality.* POCT: point-of-care test, ECG: electrocardiogram, ACS: acute coronary syndrome.

#### Follow-up contacts and outcome data

2.4.2

Two weeks after the index consultation, research staff will contact participating patients to finalize written informed consent and obtain patient-reported risk factors and outcome data. Furthermore, baseline characteristics, outcome data, and other trial data are prospectively and systematically collected for up to 6 weeks following the index consultation (Fig. 2). Outcome data for all participants, including those lost to follow-up (no follow-up outcomes available), are obtained from medical records at the patients’ general practice and from regional hospital databases. MACE and final diagnoses are adjudicated by an expert panel consisting of two general practitioners with a special interest in cardiovascular care, blinded to troponin POCT results. For verification of MACE and in the event of disagreement, a third independent expert (cardiologist) is consulted.

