### Objectives

1.2

To address this gap, we are conducting a diagnostic trial evaluating a primary care-tailored approach for ruling out ACS in OOH-PC that balances diagnostic safety and efficiency. Our primary objective is to evaluate the diagnostic performance of the *HEART-GP strategy*, which integrates a single fingerstick-obtained hs-troponin measurement with clinical assessment and an optional ECG, in terms of safety (sensitivity and negative predictive value) and efficiency (reduction in ED referrals) when used in out-of-hours primary care. The primary outcome is major adverse cardiovascular events (MACE), a composite of death, ACS, or urgent revascularization within six weeks of index presentation, reflecting the risk for cardiovascular events rather than a single clinical syndrome.

The secondary objectives are:1.To compare the diagnostic performance (safety and efficiency) of the *HEART-GP strategy* with current standard care based on (unaided) clinical judgment.2.To evaluate whether using sex-specific versus universal hs-troponin cut-off values improves safety and/or efficiency.3.To assess whether embedding hs-troponin measurements in established clinical risk scores (HEART, INTERCHEST, Marburg Heart Score) further improves diagnostic performance compared to the HEART-GP strategy alone.

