#### Symptom assessment form

2.2.2

The treating physician is asked to complete a structured, symptom-based checklist designed to standardize and document clinical assessment. The form includes symptom elements of three risk scores, namely (modified) H(E)ART, INTERCHEST and the Marburg Heart Score (Table 1). In addition, GPs are asked to record their ‘gut feeling/sense of alarm’, as well as whether they would have referred the patient based on their clinical judgement without access to the POCT result. The checklist is completed during the index consultation, instructed to be completed prior to disclosure of troponin result, to ensure unbiased responses. The form contains no recommendations or prompts regarding management decisions.

**Table 1 tbl1:** (Modified) HEART(s), Marburg Heart Score, INTERCHEST risk stratification scores.

(Modified) HEART score [16,17]		Points	Marburg Heart Score [18]		Points	INTERCHEST [19]		Points
History	Highly suspicious	2	Sex/age (Female ≥65, male ≥55 years)	Yes	1	Sex/age (Female ≥65, Male ≥55 years)	Yes	1
	Moderately suspicious	1		No	0		No	0
	Slightly suspicious	0						
ECG	Significant ST deviation	2	History of cardio-vascular disease	Yes	1	History of coronary artery disease	Yes	1
	Non-specific repolarization abnormalities	1		No	0		No	0
	Normal	0						
Age	≥65 years	2	Patient assumes the pain is of cardiac origin	Yes	1	Chest pain related to effort	Yes	1
	45 – 64 years	1		No	0		No	0
	<45 years	0						
Risk factors	History of atherosclerotic disease or ≥ 3 RF	2	Pain gets worse with exercise	Yes	1	Pain reproducible by palpation	Yes	Minus 1
	1 – 2 RF	1		No	0		No	0
	No known RF	0						
Troponin∗	≥23 ng/L (99th percentile)	2	Pain is not reproducible by palpation	Yes	1	Physician initially suspected a serious condition	Yes	1
	4-23 ng/L	1		No	0		No	0
	<4 ng/L	0						
∗Sex-specific HEARTs: sex-specific 99th percentile for troponin (male 27 ng/L, female 18 ng/L) [15]						Chest discomfort feels like pressure	Yes	1
							No	0

Table 1: *ECG: electrocardiogram, RF: risk factors for atherosclerosis, HEART: History, ECG, Age, Risk Factors, Troponin, INTERCHEST: international chest pain prediction*.

Non-specific repolarization abnormalities: LVH: left ventricular hypertrophy, LBBB: left bundle branch block or PM: pacemaker.

Risk factors: Hypertension, Hypercholesterolemia, Diabetes Mellitus, obesity (BMI >30 kg/m2), smoking, positive family history.

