History of atherosclerotic disease: prior Myocardial Infarction, Transient Ischemic Attack, Cerebrovascular accident, Peripheral Arterial disease or previous Percutaneous Coronary Intervention or Coronary Bypass graft.

Textbox 1Out-of-hours primary care in the NetherlandsIn the Dutch healthcare system, GPs serve as round-the-clock gatekeepers to secondary care, except in emergencies requiring immediate ambulance assistance and transport to the ED. OOH-PC centers operate from 17.00 to 08.00 on weekdays and throughout weekends and holidays. They are organized through regional GP cooperatives, serving patients registered with affiliated practices within a defined geographic area (Fig. 1).Upon contact with an OOH-PC center, trained triage nurses, supervised by GPs, conduct telephone triage using the Netherlands Triage Standard (NTS), a standardized, symptom-driven protocol that assigns an urgency level to each case [20]. Although the NTS provides a structured framework, triage nurses or supervising GPs may adjust the final urgency classification based on additional contextual information. This can include the patient's perceived level of distress or whether there were repeated calls for the same symptom within a short timeframe.Patients classified as high urgency are referred directly to the ED without GP assessment. Those with the lowest urgency level receive self-care advice, or are advised to contact their own GP during regular office hours. Patients triaged as intermediate urgency are assessed by a GP at the OOH-PC facility, where they may be treated on-site, referred to the ED for further evaluation, or discharged with appropriate safety-netting advice [21].Alt-text: Textbox 1Textbox 2Why we use major adverse cardiovascular events (MACE)The primary outcome of MACE, a composite of ACS, urgent revascularization, or all-cause death/mortality at 6 weeks follow-up, is an outcome that is patient-centered, objective, and delayed, serving as a suitable reference standard in urgent primary care where not all patients undergo the same in-hospital diagnostic work-up. Using MACE rather than ACS avoids circularity with the index diagnosis and reduces verification bias. It provides a comprehensive and clinically meaningful measure of cardiovascular risk, enhances statistical power, and aligns with established regulatory and methodological standards. All events will be adjudicated with blinding to the index test, with prespecified sensitivity analyses, on the individual components of MACE, performed.Alt-text: Textbox 2

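### HEART risk factors appear to be asked two weeks after the index visit, alongside outcomes and with no stated pre-index reference date, so later diagnoses could favour HEART over HEART-GP in secondary objective 3

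*Protocol article*

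**What the plan says.** Secondary objective 3 (1.2 Objectives) is "To assess whether embedding hs-troponin measurements in established clinical risk scores" and thereby improves on the HEART-GP strategy alone. The scores are HEART, INTERCHEST and the Marburg Heart Score.

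The score inputs are described in two places.

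- **Index form (2.2.2).** "The form includes symptom elements of three risk scores, namely (modified) H(E)ART, INTERCHEST and the Marburg Heart Score". On timing, "The checklist is completed during the index consultation, instructed to be completed prior to disclosure of troponin result". The patient text under Fig. 4 likewise announces extra questions about symptoms only.
- **Follow-up (2.4.2).** "Two weeks after the index consultation, research staff will contact participating patients" to complete written consent and to "obtain patient-reported risk factors and outcome data". The section continues that "baseline characteristics, outcome data, and other trial data are prospectively and systematically collected for up to 6 weeks following the index consultation".

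Table 1 gives the HEART risk-factor item 0, 1 or 2 points. One or two risk factors score 1; three or more, or atherosclerotic disease, score 2. Six factors count: hypertension, hypercholesterolemia, diabetes, obesity, smoking and family history. Marburg and INTERCHEST have no risk-factor item. Each has one history item worth 1 point.

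**The concern.** A score meant for use at the index consultation should be built from what could be known then. The only timing given for risk-factor collection is two weeks later, in the same contact that collects outcomes. By then many patients with an event will have had a hospital work-up, and hypertension, hypercholesterolemia or diabetes may have been diagnosed for the first time. If these count, part of the score is measured after the outcome and by staff who may know it.

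The HEART-GP strategy rests on the troponin result, clinical assessment and optional ECG at the visit, so it cannot gain in this way. The comparison in secondary objective 3 could therefore credit HEART with hindsight. The planned AUC comparison (DeLong) and the NRI both respond to upward moves among events. Such a gain would not recur in practice, where the GP has only pre-visit information.

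The article guards against this elsewhere: the checklist precedes disclosure of the troponin result, and adjudicators are blinded to it. It states no such guard for the risk factors.

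**Working it through.** **1. The plan's own figure.** Inputs from 2.6.1: sensitivity 98%, margin 3%, alpha 0.10 two-sided (z = 1.645), MACE prevalence 7%.

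Cases = z² × 0.98 × 0.02 / 0.03² = 58.92; N = 58.92 / 0.07 = 841.7, rounded up to 842. This reproduces the stated number and is not touched by this point. At 900 participants, 0.07 × 900 = 63 MACE cases are expected.

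**2. Where each item comes from.**

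| Item | Scores using it | Stated source and time |
|---|---|---|
| Symptom elements | all three | GP form at index, before the troponin result |
| Risk factors | HEART only | patient report at two weeks, with outcomes |
| Cardiovascular history | all three | not stated |

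Only the middle row has a late time attached to it. That the two-week answers feed the HEART item is inferred from the index form being described by its symptom content.

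**3. What one late diagnosis does under Table 1.** Take age 55 (1), moderately suspicious history (1), normal ECG (0), troponin below 4 ng/L (0) and no known risk factor (0): HEART = 2. One factor first diagnosed after the visit makes HEART = 3. A patient with two known factors moves from 1 to 2 on the item. A patient with one known factor does not move.

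**4. Illustration of direction and size.** All inputs in this step are assumptions, not trial figures. Items are independent given MACE status; probabilities are for 0, 1 and 2 points.

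| Item | MACE | No MACE |
|---|---|---|
| History (symptoms) | 0.20, 0.40, 0.40 | 0.55, 0.35, 0.10 |
| Age | 0.08, 0.42, 0.50 | 0.35, 0.40, 0.25 |
| Troponin | 0.05, 0.35, 0.60 | 0.65, 0.30, 0.05 |
| Risk factors | 0.15, 0.45, 0.40 | 0.35, 0.45, 0.20 |

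AUC = P(MACE score > non-MACE score) + 0.5 × P(tie). For the risk-factor item alone: 0.45×0.35 + 0.40×0.80 + 0.5×(0.15×0.35 + 0.45×0.45 + 0.40×0.20) = 0.645. Summing the four items (HEART without ECG) gives 0.912.

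(a) A share of the MACE patients below 2 points moves to 2 points, with no change in the others:

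| Share moved | Cases of 63 | Item AUC | HEART AUC |
|---|---|---|---|
| 0% | 0 | 0.645 | 0.912 |
| 10% | 3.8 | 0.671 | 0.917 |
| 25% | 9.5 | 0.709 | 0.925 |
| 50% | 18.9 | 0.773 | 0.939 |
| 100% | 37.8 | 0.900 | 0.966 |

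(Cases = 63 × 0.60 × share.) This overstates the effect of a single new diagnosis, which adds at most one point. With 25% of MACE patients gaining one point, the item distribution is 0.1125, 0.375, 0.5125 if every 1-point patient had two factors (item AUC 0.697, HEART 0.923). It is 0.1125, 0.4875, 0.40 if none had (item AUC 0.660, HEART 0.916).

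(b) Patients without MACE gain diagnoses too. Keep 25% moved to 2 points in MACE and move a share of the non-MACE patients below 2 points in the same way:

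| Share moved, no MACE | Item AUC | HEART AUC |
|---|---|---|
| 0% | 0.709 | 0.925 |
| 10% | 0.665 | 0.916 |
| 25% | 0.600 | 0.901 |

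The item AUC returns to 0.645 when about 14.7% of the non-MACE patients below 2 points move: (0.70875 − 0.645) / 0.43375, where 0.43375 is the fall per unit share. HEART gains only if new diagnoses are clearly more frequent in MACE cases.

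**The case against.** The strongest reply is that this is an article, not the full protocol. Its data management section says that operating procedures and a data management plan exist, and questionnaire wording or an extraction date rule would normally sit there. The form is said to include symptom elements, which does not exclude others, and nothing states that the scores use the two-week report. This limits confidence but does not remove the point: the article does not merely leave the timing open, it gives a late one and pairs it with outcome collection.

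Three stronger readings are tempting and are not supported.

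- **All three scores are contaminated.** Marburg and INTERCHEST contain no risk-factor item, and the article does not say when or from whom history is taken.
- **The index infarction or PCI becomes a HEART point.** The Table 1 note reads "History of atherosclerotic disease: prior Myocardial Infarction, Transient Ischemic Attack" and goes on to previous PCI. In ordinary use, prior and previous exclude the index episode. Only the risk factors lack such a limit, and of the six, obesity, smoking and family history are unlikely to be new findings of a cardiac work-up.
- **A definite gain in sensitivity follows.** Lifting 3 of 63 cases over a cut-off would add 4.8 points, but the 3 has no source and no HEART cut-off is printed. The 3% margin in 2.6.1 is the precision of the index-test estimate, not a yardstick for comparing scores.

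Referred patients without MACE also count against a simple upward bias. If the 40-70% referral quoted in the background applied, 360 to 630 of 900 would be referred, leaving at least 360 − 63 = 297 without MACE who could also acquire diagnoses. That stands, and is why no net figure is claimed.

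**Conclusion.** The point holds in a limited form. As described, HEART risk factors appear to be collected two weeks after the index visit, together with outcomes and inside the outcome window, without a stated pre-index reference date. That is a procedure open to bias in favour of HEART over HEART-GP in secondary objective 3. It rests on two assumptions: that the two-week answers are the source of the item, and that new diagnoses are more frequent in MACE cases than in others. Both are plausible; neither is shown. The direction is probably upward for HEART, but the size and net effect cannot be derived from the documents.

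The primary analysis of the HEART-GP strategy and the sample size are unaffected. Confidence is moderate, because the full protocol and case report form are not shown and may already anchor the items. If they do, one sentence settles the matter. Otherwise the change should be made before the scores are computed.

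**What to change.** State the source and reference date of every score item. Score the HEART risk factors, and the history items of all three scores, only from information dated before the index consultation, excluding the index episode. Extract them from the general-practice records that the trial already accesses for outcomes, by someone without sight of the outcome. Word the two-week question so that it asks about the time before the day of the visit. Use unanchored two-week reports only in a sensitivity analysis.

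The cost is small: a date rule on records already accessed, which can also be applied to patients already enrolled, and a change of questionnaire wording. The drawback is that factors known to the patient but absent from the record, such as family history or smoking, may be scored as absent. The anchored patient report can supplement those items.

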#### HEART-GP strategy incorporating hs-troponin testing (index test)

2.2.1

The intervention involves the HEART-GP strategy (Fig. 3), which combines a single point-of-care high-sensitivity troponin measurement, with clinical assessment and optional ECG. We use the Siemens Atellica VTLi hs-troponin POCT to measure hs-troponin levels from a fingerstick blood sample, which returns results within 8 min. For ethical reasons, the GP is not blinded to the hs-troponin results during the consultation. The specifics of this assay are described elsewhere in further detail, but in essence the whole blood Limit of Detection is 1.6 ng/L and the Limit of Quantitation at 10% CV is 8.9 ng/L [14]​. The non-sex specific 99th percentile upper reference limit for this assay is 22.9 ng/L [15]. In our study we applied a lower decision threshold of ≥4 ng/L for rule out purposes, as evidence from prior studies show a sensitivity of 98.8% and a NPV of 99.8% for ruling out ACS in low-risk populations at the emergency department (ED) [11,15].

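### The promised blinding to the index test (the HEART-GP strategy) becomes blinding to the POCT result alone in the outcome section, leaving a possible upward bias in sensitivity and NPV

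*Protocol article*

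**What the plan says.** The heading of Section 2.2.1 attaches the label index test to the HEART-GP strategy, and the text says that the strategy "combines a single point-of-care high-sensitivity troponin measurement, with clinical assessment and optional ECG". Section 2.4.1 gives three grounds for advised urgent referral under the strategy, any one of which is enough: high clinical suspicion of ACS, a POCT value of 4 ng/L or more, or an abnormal ECG where one was made. Sections 1.2 and 2.6 make the strategy, not the POCT alone, the object of the primary analysis.

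On blinding there are two statements. Textbox 2: "All events will be adjudicated with blinding to the index test". Section 2.4.2: the panel consists of "two general practitioners with a special interest in cardiovascular care, blinded to troponin POCT results". The same section adds: "For verification of MACE and in the event of disagreement, a third independent expert (cardiologist) is consulted". It does not say what that expert is blinded to.

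Outcome data come from the patients' "general practice and from regional hospital databases". Section 2.2.1 says that "the GP is not blinded to the hs-troponin results during the consultation". Section 2.3 includes unstable angina in ACS, and so in MACE.

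**The concern.** The general promise covers three components and the operative rule names one. Clinical suspicion alone can make a patient strategy-positive, so an adjudicator who knows the index GP's impression knows part of the index test result.

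This matters most where the outcome is a judgement. Unstable angina is the clearest case. Textbox 2 itself accepts that in-hospital work-up differs between patients. For someone kept in primary care, the panel may have little beyond primary-care notes, and a low-suspicion index assessment could weigh on the call. Missed events have to be found in that group. If some are not called, sensitivity and NPV, the two primary safety measures, both look better than they are.

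The POCT value could also reach the panel indirectly. The treating GP knows it and is advised to refer on it, so it can appear in a referral or discharge letter.

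**Working it through.** **1. The passages side by side.**

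| Place | What it covers |
|---|---|
| Section 2.2.1, heading and text | Index test = POCT + clinical assessment + optional ECG |
| Textbox 2 | All events, blinded to the index test |
| Section 2.4.2, two GPs | Blinded to POCT results |
| Section 2.4.2, cardiologist | Blinding not stated |

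If index test in Textbox 2 means the strategy, Section 2.4.2 is narrower than the promise. If it means the POCT, the two blinding statements agree, but the clinical part of the strategy is not covered, and the usage conflicts with the heading of Section 2.2.1. Both readings call for a correction.

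**2. The plan's own figure.** Inputs from Section 2.6.1: sensitivity 0.98, margin 0.03, two-sided alpha 0.10, MACE prevalence 7%.

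Events = 1.645² × 0.98 × 0.02 / 0.03² = 58.92. N = 58.92 / 0.07 = 841.7, rounded up to 842. This reproduces the stated number, and nothing here disputes it.

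**3. Expected events.** 900 × 0.07 = 63.

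**4. Effect of one changed call.** Adjudication does not alter the index result; it adds or removes a MACE. The two directions differ sharply.

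- A missed event is not called: 62/63 = 98.41% becomes 62/62 = 100%, a rise of 1.59 points.
- An extra event is called in a strategy-positive patient: 62/63 = 98.41% becomes 63/64 = 98.44%, a rise of about 0.02 points. Starting from 60/63, it is 61/64 = 95.31% against 95.24%, about 0.07 points.

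NPV uses strategy-negative patients only, so the first kind of change raises it and the second leaves it unchanged.

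**5. Two dropped events (assumed counts).** 60/63 = 95.2% becomes 60/61 = 98.4%, a rise of 3.1 points, from below the 98% target to above it.

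**6. A range (assumed values).** With true sensitivity s and a fraction m of missed events not called, the observed value is s / [s + (1 − s)(1 − m)].

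| s | m = 0 | m = 0.25 | m = 0.50 |
|---|---|---|---|
| 0.90 | 0.900 | 0.923 | 0.947 |
| 0.95 | 0.950 | 0.962 | 0.974 |

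The documents give no value for m, and m = 0 is possible.

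**The case against.** A reader might infer that adjudicators see the assessment form and that sensitivity is therefore biased upward. The documents do not support that. Section 2.4.2 names what the panel is blinded to; it does not say that anything else is shown. Textbox 2 can be read as the general rule, with all events extending to the cardiologist. The term index test is also not used uniformly: Section 2.6.1 takes its target sensitivity from studies of a single troponin measurement. These points stand. They make the exposure possible, not demonstrated. They do not remove the mismatch, because neither reading of the term puts the clinical component clearly under the stated blinding.

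A reader might also infer that every influenced call is worth 1.6 points and that two calls use up the 3% margin. Only a dropped missed event has that effect. At the 98% target, 63 events imply about 1.3 misses (63 × 0.02), so two dropped misses presuppose a lower true sensitivity. The 3% is a precision half-width for the sample size, not an allowance for bias.

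Safeguards limit the exposure. Death is not open to this bias, and MI and revascularization are less open than unstable angina. Textbox 2 plans analyses of the individual MACE components, Section 2.3 lists MI and all-cause death as separate outcomes, two assessors adjudicate, and a cardiologist verifies. These help to show whether results depend on unstable angina, but they do not protect the primary composite.

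Symptoms and ECG are needed to adjudicate ACS, so blinding to all clinical data is hardly feasible. That is right, and it shapes the fix. The same leakage would favour the unaided-judgement comparator too, so no net advantage to HEART-GP follows for that comparison.

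Finally, redaction procedures are details that an article may leave to the full protocol or operating procedures. Their absence is not the point; the point is that two stated blinding rules differ in scope.

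**Conclusion.** The point holds as a mismatch with a possible consequence. Followed literally, Section 2.4.2 lets the index GP's suspicion, and a POCT value quoted in the records, inform judgement-based ACS calls. The likely direction is upward for sensitivity and NPV. The size cannot be derived from the documents: it is zero if adjudicators are not influenced, and about 1.6 points of sensitivity for each missed event left uncalled, given 63 expected MACE. Over-calling in strategy-positive patients has almost no effect.

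This rests on 900 participants, a 7% prevalence, and reading strategy-positive as any one of the three grounds in Section 2.4.1. With so few missed events expected, a small effect could matter for the main safety claim, so the correction is worth making.

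**What to change.** Align Section 2.4.2 with Textbox 2, and use index test in one sense throughout. State that all adjudicators, including the cardiologist, are masked to:

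- the POCT value, also where a referral or discharge letter quotes it;
- the strategy classification;
- the index GP's suspicion, sense-of-alarm and would-refer entries.

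Keep presenting symptoms, ECG tracings, GP follow-up records and hospital data in the packet. A packet built mainly on hospital data would make events harder to find in patients who were not referred, which is where missed events lie.

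Record each case in which masking failed and repeat the primary analysis without those cases as a sensitivity analysis. Failures may cluster in referred patients, so the repeat is a check on robustness and not a replacement estimate. Enrolment began in March 2023; if some events have already been adjudicated, apply the same record to them.

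The cost is revised wording and redaction when packets are prepared. No extra assessor is needed, and the sample size is unchanged.
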